### Secondary endpoints

Secondary endpoints include:

- AFF that develops more than 7 days post-surgery and until hospital discharge.

- AFF in patients who do not undergo cardiac surgery during ICU stay, the first week after ICU discharge, until hospital discharge.

- The time course of the incidence of AFF (in cardiac-surgery patients and total patient group).

- The incidence of other serious arrhythmias that require immediate medical intervention (in cardiac-surgery patients and total patient group).

- Time that potassium is in the 3.5-5.0 mmol/L reference range during ICU-admission (in cardiac-surgery patients and total patient group).

- The occurrence of distinct hypokalemia (i.e potassium <2.8 mmol/L) and distinct hyperkalemia (i.e. potassium >6.0 mmol/L) in cardiac-surgery patients and the total patient group, also a safety endpoint.

- Level of glucose control and insulin requirements during ICU admission.

- Biochemical disturbances of electrolytes (sodium, magnesium and calcium), blood gas analysis, lactate and renal function (creatinine, urea) during hospital admission (total patient group).

- Cumulative fluid balance during ICU admission (patients admitted to the ICU for more than 5 days).

- ICU and hospital length of stay (in cardiac-surgery patients and total patient group).

- ICU-mortality and hospital mortality (in cardiac-surgery patients and total patient group, also a safety endpoint) as well as 90-day, and 1 year mortality.

In addition to the cardiac surgery group and the total patient group, the following subgroups will also be compared:

- Patients who underwent CABG with the use of cardiopulmonary bypass versus patients who underwent CABG without cardiopulmonary bypass.

- Patients with a history of AFF prior to surgery versus patients without a history of AFF prior to surgery.

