### Primary endpoint

The primary endpoint is the incidence of in-hospital atrial fibrillation or atrial flutter (denoted by AFF), confirmed by a 12-lead electrocardiogram (ECG), in patients after cardiac surgery. The reference period over which this primary endpoint is determined is the first 7 days post-surgery, or until hospital discharge if the patient is discharged earlier. The presence of AFF is established by evaluation of all electrocardiograms by independent and qualified cardiologists who are blinded to the treatment allocations.

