### Data collection

Baseline patient characteristics are collected at ICU admission (age, sex, length, weight, medical history, medication use, reason of admission). If a patient undergoes (cardiac) surgery, data concerning the procedure and the duration of the procedure (and the time on cardiopulmonary bypass) are collected. For cardiac surgery patients the EuroSCORE model for operative risk stratification is calculated [37]. In non-cardiac surgery patients the APACHE II score is used [38].

This trial requires no specific tests or procedures that are not regularly performed. Daily laboratory tests and blood gas analysis (daily at the ICU, in the general ward only when deemed necessary by the physician) are all part of standard care. During ICU admission all patients are under continuous rhythm monitoring (3-lead) and a 12-lead ECG is done at admission (in cardiac-surgery patients also after 24 and 48 hours), and is repeated when arrhythmias or other complications occur or are suspected. At the general ward a the rhythm is checked regularly and a 12-lead ECG is performed at admission, when deemed necessary by the attending physician, and at discharge. When a patient is prone for severe arrhythmias, continuous monitoring by telemetry is continued at the general ward. All in-hospital ECGs of the included patients are evaluated by the physicians at the ICU and the general ward as well as by independent cardiologists who are blinded for the potassium control-targets.

Potassium and glucose control data (potassium and glucose levels, amount of potassium chloride and insulin administration, number of measurements per day) are automatically stored by the GRIP-II program. All other laboratory tests are stored in the hospital information system. ICU-parameters such as the amount of fluid administered, the use of vasoactive drugs, anti-arrhythmic drugs, diuresis, and the fluid balance are monitored and collected. Minor complications and major complications (e.g. death, stroke, myocardial infarction, organ failure and major bleeding complications) are recorded. Mortality is recorded for the ICU, during hospitalisation and at 90-days. Follow-up information will be obtained from hospital records and the central personal records database.

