### Statistical analysis

To compare groups, the Student's t test (normally distributed variables), the Mann-Whitney U test (other continuous variables) or Fisher's exact test (categorical variables) will be used when appropriate. The level of potassium control will be expressed as the time within the normokalemic range (3.5 - 5.0 mmol/L) divided by the total time spent on the ICU.

In multivariate analysis we will investigate the interaction with glucose, the amount of administered insulin, sodium and magnesium. A two-sided P value of <0.05 will be considered significant. The Statistical package for the social sciences (SPSS) version 16.0 will be used for all statistical analysis.

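### In patients without cardiac surgery, AFF is counted over periods that end with ICU or hospital stay, so a difference in stay between arms can pass for a difference in AFF

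*Protocol article*

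**What the plan says.** Under Secondary endpoints, the Protocol article lists "AFF in patients who do not undergo cardiac surgery during ICU stay, the first week after ICU discharge, until hospital discharge". The wording does not settle whether these are three separate periods, cumulative periods or one period. The Abstract describes the same endpoint simply as in-hospital AFF in medical and non-cardiac-surgery patients.

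For cardiac-surgery patients, the Primary endpoint section sets a window that "is the first 7 days post-surgery, or until hospital discharge if the patient is discharged earlier". AFF after day 7 and up to hospital discharge is a separate secondary endpoint for them.

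Three other statements bear on the point:

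- Length of stay is itself an outcome: "ICU and hospital length of stay (in cardiac-surgery patients and total patient group".
- Rhythm surveillance changes at ICU discharge. In the ICU, "During ICU admission all patients are under continuous rhythm monitoring (3-lead) and a 12-lead ECG is done at admission". On the ward, a "12-lead ECG is performed at admission, when deemed necessary by the attending physician, and at discharge", with telemetry only for selected patients (Data collection).
- The Statistical analysis section gives a general list of tests, in which "Fisher's exact test (categorical variables) will be used when appropriate". It mentions no allowance for differing time at risk.

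**The concern.** A proportion with AFF is comparable between arms only if the arms are observed for similar lengths of time, or if the analysis allows for the difference. Here the observation period ends, or in one case begins, at a discharge that follows allocation and that the trial treats as an outcome. A patient with a 2-day ICU stay contributes 2 days to AFF during ICU stay; a patient with a 20-day stay contributes 20.

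If one potassium target lengthened or shortened stay, the AFF comparison in these patients would mix an effect on rhythm with an effect on stay. AFF may also prolong stay, in which case the window depends on the event it counts. Closer monitoring in the ICU would push in the same direction as longer time at risk. What is at stake is the reading of one secondary endpoint in about a quarter of the trial.

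**Working it through.** **The plan's own figures.** No sample size or expected rate is given for this endpoint, so there is no figure to reproduce for it. The Sample size calculation section assumes that about 75% of admissions follow cardiac surgery. That leaves 25% × 1200 = 300 patients, or about 150 per arm. The primary calculation does reproduce: 50% versus 40%, two-sided 5%, 80% power gives 388 per arm (408 with continuity correction) against the stated 400. It does not depend on the endpoint discussed here.

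**The windows side by side.**

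| Period, patients without cardiac surgery | What bounds it |
|---|---|
| During ICU stay | Length set by ICU stay |
| First week after ICU discharge | Start set by ICU discharge; exists only for those who leave the ICU alive |
| Until hospital discharge | If it means the whole admission, length set by hospital stay |

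For cardiac-surgery patients the primary window is at most 7 days from surgery. It can be shortened by hospital discharge but does not depend on ICU discharge.

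**Illustration.** Assume the same constant daily hazard h in both arms, so the target has no effect on AFF. Incidence by day t is 1 − exp(−h × t). The hazards and the ICU stays of 4 and 5 days are assumptions, because the document gives neither.

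| h per day | 4 days | 5 days | Gap (points) | Events per 150 |
|---|---|---|---|---|
| 1% | 1 − exp(−0.04) = 3.9% | 1 − exp(−0.05) = 4.9% | 1.0 | about 1.4 |
| 3% | 1 − exp(−0.12) = 11.3% | 1 − exp(−0.15) = 13.9% | 2.6 | about 4 |
| 5% | 1 − exp(−0.20) = 18.1% | 1 − exp(−0.25) = 22.1% | 4.0 | about 6 |

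**Front-loaded risk.** With 8% per day to day 3 and 1% per day after that (assumed), 4 days gives 1 − exp(−0.25) = 22.1% and 5 days gives 1 − exp(−0.26) = 22.9%. The gap shrinks to 0.8 points; the direction is the same.

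**Cumulative reading, ICU stay plus 7 days.** At 3% per day, 11 versus 12 days gives 1 − exp(−0.33) = 28.1% versus 1 − exp(−0.36) = 30.2%, a gap of 2.1 points.

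**Whole-admission reading.** The same formula applies with hospital stay as t. ICU stay no longer sets the length; it acts only through closer monitoring while the patient is in the ICU.

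**With a 7-day window from ICU admission.** Incidence is 1 − exp(−7h) in both arms whatever the ICU stay: 6.8%, 18.9% and 29.5% at 1%, 3% and 5% per day. The gap is zero, given equal detection and no death or hospital discharge before day 7.

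**The case against.** The strongest reply is that the sentence continues to hospital discharge and the Abstract calls the endpoint in-hospital AFF. Read that way, the measure is AFF over the whole admission, reported by phase, and ICU stay does not set its length. This stands. A reader might infer that a difference in ICU stay alone must change AFF incidence; the documents support that only for the ICU-stay period and for a cumulative reading ending a week after it. Under the whole-admission reading the dependence moves to hospital stay, which is also a post-allocation outcome and a listed endpoint.

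Second, the primary window is itself cut at hospital discharge, so it is not a fully fixed clock. That is correct, and the contrast is one of degree: at most 7 days, against no upper limit on ICU or hospital stay.

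Third, no test is assigned to this endpoint, and the handling of time at risk may be set out in an analysis plan that is not shown. This is fair. The point is therefore about how the window is defined, not about a missing method.

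Fourth, the potassium target applies until discharge to the ward, so the ICU period is the time on the intervention, and medical patients have no surgery date to count from. The rationale is reasonable, but the trial's own primary endpoint already runs past ICU discharge, and ICU admission supplies a start date for everyone.

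A reader might also infer that the two patient groups' clocks cannot be combined in "The time course of the incidence of AFF (in cardiac-surgery patients and total patient group". The documents do not support this: they do not say that the time course is built from these windows. Its time origin is simply not stated, and one common to all patients could be chosen.

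Finally, the effect is small. At 3% per day, about 21 versus 17 events in 150 per arm gives a Fisher p-value of 0.60, and a true gap of that size would reach significance only about 10% of the time.

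**Conclusion.** The point holds in a limited form. On each reading, the AFF observation period in patients without cardiac surgery is set by ICU or hospital discharge, a post-allocation event tied to a listed endpoint. If stay differs by arm, AFF proportions can differ with equal daily risk. For a one-day difference in ICU stay (4 versus 5 days), the gap during ICU stay is about 1.0 to 4.0 points over assumed constant hazards of 1% to 5% per day, and 0.8 points in the front-loaded example.

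The bias arises only if stay differs by arm, which the protocol neither assumes nor excludes. The hazards and stays are illustrative. The issue is minor: one secondary endpoint in about 25% of patients, with no effect on the primary endpoint or the sample size.

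**What to change.** Make the compared measure AFF within 7 days of ICU admission, which is when the target is allocated, capped at hospital discharge. Report AFF after day 7 up to hospital discharge as a separate measure, mirroring the split already used for cardiac-surgery patients. Keep the ICU and ward breakdown as description.

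The cost is a change of wording; the same ECGs and dates serve. The downside is that late AFF in long-stay patients moves to the separate measure. The change does not remove everything: the cap at hospital discharge and the difference in rhythm monitoring between ICU and ward both remain and should be acknowledged when the result is interpreted.

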## Methods/Design

The GRIP-COMPASS trial is a single-center, prospective trial with alternating blocks of patients with blinded evaluation of the primary endpoint. Twelve hundred patients are assigned to the NLP control-target of 4.0 mmol/L or the NHP control-target of 4.5 mmol/L at ICU admission (Figure 1). Allocation to an arm is alternated in blocks of approximately 50 patients until 1200 patients are included, resulting in 24 blocks (Figure 2). Informed consent for inclusion into one of the two study arms was waived by our institutional review board since in both the NLP arm and the NHP arm standard potassium treatment is involved with the only difference that the two therapeutic strategies aim at differing normal levels.

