### Inclusion

All patients admitted to the thoracic ICU are considered eligible for inclusion. Excluded are those patients who do not have a central venous catheter or an enteral feeding tube because such patients are not entered into the GRIP-II program for potassium regulation since they cannot receive continuous potassium administration to the extent that is regularly necessary. Only rarely will patients be excluded for this reason. Immediately after admission a patient is assigned a potassium control-target that remains unchanged for that patient until discharge to the general ward. The general characteristics of the population admitted to the thoracic ICU are summarized in table 1. The majority of patients (~75%) are admitted after cardiac surgery, i.e. coronary artery bypass surgery (CABG) and/or valve repair.

**Table 1 T1:** General characteristics of expected patient cohort.

	Thoracic ICU
	n = 500
Age (years), median (IQR)	66 (57-74)
Male sex	69%
APACHE II, median (IQR)	14 (10-18)
Reason for admission	
Cardiac surgery	75%
Cardiac arrest	9%
Other surgery	10%
Medical	5%
Miscellaneous	3%
post-operative AFF*	50%
In-hospital mortality	8%

*after cardiac surgery

Baseline characteristics of a recent cohort of 500 patients that were admitted to the thoracic ICU, to provide an impression of the expected patient population in the GRIP-COMPASS trial. The incidence of AFF was observed in a subgroup of 150 consecutive cardiac surgery patients. Abbreviations used in table: ICU intensive care unit; IQR interquartile range; APACHE II acute physiology and chronic health evaluation II score; AFF atrial fibrillation and atrial flutter.

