### Sample size calculation

Because the incidence of AFF in patients after cardiac surgery is the primary endpoint, the incidence recently measured in these patients and the expected potential difference in this incidence between the NLP and NHP groups were the main determinants of the power analysis. In a pilot study of 150 consecutive patients admitted after open-heart surgery (CABG and/or valve replacement) during a 3-month period, we observed that 50% developed postoperative AFF at the ICU or at the ward. To detect a 10% reduction in the incidence of AFF, with a two-sided level of significance of 5% and a power of 80%, 2 × 400 cardiac surgery patients should be included. Assuming that approximately 75% of the admitted patients will undergo cardiac surgery and with a 10% margin for excluded patients we arrived at a target number of 1200 consecutive patients admitted to the ICU to be included.

In a previous analysis of potassium regulation with GRIP-II, patients reached a stable potassium level within 12 hours with a mean ± standard deviation (SD) level of 4.25 ± 0.36 mmol/L [20]. When we assume that GRIP-II maintains this level of accuracy, then a significant difference in plasma potassium between the NLP and NHP groups will be found with less than 50 patients. Thus we do expect to easily detect very significant differences in the potassium levels between the NLP and NHP groups.

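### Minor: ICU and hospital length of stay are compared as plain durations, so a stay cut short by death counts as a short stay

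*Protocol article*

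**What the plan says.** The Secondary endpoints section of the protocol article lists "ICU and hospital length of stay (in cardiac-surgery patients and total patient group"). The populations are thus all cardiac-surgery patients and everyone in the trial. The same list does narrow a population where that was wanted: cumulative fluid balance is confined to patients with an ICU stay above 5 days. Length of stay carries no such limit and no rule for patients who die.

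The Statistical analysis section gives one general rule for comparing groups. After the t test for normally distributed variables it continues: "the Mann-Whitney U test (other continuous variables) or Fisher's exact test (categorical variables) will be used when appropriate". No time-to-event or competing-risk method is named.

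Table 1, in the Inclusion section, reports "In-hospital mortality 8"% for a recent cohort of 500 thoracic ICU patients. Mortality has its own entry among the secondary endpoints: "ICU-mortality and hospital mortality (in cardiac-surgery patients and total patient group, also a safety endpoint) as well as 90-day, and 1 year mortality".

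**The concern.** A shorter stay is usually read as the better outcome. In a plain comparison of durations, a stay that ends in death is scored like one that ends in going home, so a death on the first day receives one of the shortest, most favourable ranks. If one potassium target led to more early deaths, that arm's stays would look shorter. The length-of-stay result would then lean against the mortality endpoints listed next to it.

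**Working it through.** **The plan's own figures.** The article gives no figure for length of stay. Its primary sample size reproduces: 50% v 40%, two-sided 5%, 80% power gives 388 per arm, or 408 with continuity correction, against the stated 400. Inflation gives 800/0.75/0.9 = 1185 or (800/0.75) × 1.1 = 1173, against 1200. This point does not affect those numbers.

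**Inputs from the article.** 1200 patients in two arms, taken as 600 each ("Allocation to an arm is alternated in blocks of approximately 50 patients until 1200 patients are included, resulting in 24 blocks"); two-sided 5% level; 8% in-hospital mortality. Expected deaths: 0.08 × 1200 = 96, about 48 per arm.

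**Inputs that are assumptions.** The article gives no expected mortality difference, no time to death and no distribution of stay. I take mortality splits centred on 8% (6% v 10%; 7% v 9%), the same stay distribution for survivors in both arms (lognormal, median 9 days), and independent patients.

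**Index.** P is the probability that a random patient in the lower-mortality arm stays longer than one in the higher-mortality arm. Above 0.50, the raw comparison favours the arm with more deaths.

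**Extreme case: every death precedes every live discharge.** With mortality a in the lower arm and b in the higher arm,

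P = (1−a)(1−b)/2 + (1−a)b + ab/2, which simplifies to 0.5 + (b−a)/2.

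The standard error is √(1201/(12 × 600 × 600)) = 0.0167.

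- 6% v 10%: 0.423 + 0.094 + 0.003 = 0.520; z = 0.020/0.0167 = 1.20; rejection probability 22.4%.
- 7% v 9%: P = 0.510; z = 0.60; rejection probability 9.2%.

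**Deaths spread over time, 6% v 10%, simulated Mann-Whitney, 600 per arm.**

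| Time to death | P, raw stay | Rejection, raw stay |
|---|---|---|
| Exponential, mean 4 days | 0.513-0.515 | 12-15% |
| Exponential, mean 9 days | about 0.505 | 6-7% |
| Exponential, mean 15 days | about 0.50 | 5% |
| Lognormal, median 2 days | 0.516 | 15% |
| Lognormal, median 4 days | 0.510 | 8% |
| Lognormal, median 9 days | 0.500 | 5% |
| Lognormal, median 15 days | 0.492 | 7% |

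The exponential rows with mean 4 and 9 days cover survivor log-SDs from 0.4 to 0.8. The lognormal rows use log-SD 0.6 for survivors and 1.0 for deaths.

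**Deaths given the worst rank.** P is about 0.48 in every row: the comparison always leans against the arm with more deaths.

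**Equal mortality, 8% v 8%.** P = 0.50 and rejection is about 5% by either analysis. There is no bias.

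**The case against.** - **The article is a condensed document.** Its analysis plan is not shown, and the handling of deaths in a secondary duration is often left there. This limits the weight of the point but does not remove it, because the article itself names both the populations and the tests, and together they give the ordering described. The words allowing tests to be used when appropriate do not bring in a different type of analysis.
- **The article gives length of stay no direction.** It is not called a measure of benefit and could simply describe bed use. A reader might infer that a shorter stay in the arm with more deaths would be reported as a benefit. The documents do not support that: mortality is reported in the same two populations and labelled a safety endpoint.
- **A misleading pair of results would be rare.** With 6% v 10% mortality and exponential deaths averaging 4 days, Fisher's test on mortality is significant in about 70% of simulated trials. Length of stay significantly favours the worse arm while mortality is not significant in about 1.7%, or about 3.7% at 7% v 9%. This stands, and is the main reason the point is minor.
- **The 22% is an upper extreme.** It needs every death to precede every live discharge, which is implausible for ICU stay, where uncomplicated patients leave early.
- **It is tempting to say that the scale is wrong for about 1 patient in 12.** That turns the 8% into a count of misranked patients. Only deaths earlier than typical discharge are ranked favourably. The 8% also covers the whole cohort, including cardiac arrest and medical admissions; no rate is given for cardiac surgery, one of the two populations compared.

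**Conclusion.** The point holds as a minor one on a secondary endpoint. As the article states the populations and tests, a stay ended by death is scored as a short stay, and the raw comparison can lean towards the arm with more deaths. Two conditions are needed together: mortality must differ between arms, and deaths must come before typical discharge. The article predicts neither.

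With a four-point mortality difference and a mean time to death of 4 days, the index is about 0.51 and 12-15% of trials reject instead of 5%. The other time-to-death assumptions give 5% to 15%, and 22% is reached only in the extreme case. With late deaths the lean vanishes or reverses, although raw stay then still conveys little of the mortality difference. All these sizes rest on assumed mortality splits and stay distributions; only the 8% and the patient numbers come from the article. Nothing here touches the primary endpoint, the sample size or the mortality endpoints.

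**What to change.** Make the between-arm comparison time to discharge alive, once from the ICU and once from hospital, and name one method before the arms are compared:

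- Mann-Whitney on length of stay with deaths before the relevant discharge given the worst rank; or
- cumulative incidence of live discharge, with death as a competing event.

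These lean the same way but are not the same analysis, so the choice should be fixed in advance. Show raw length of stay descriptively, overall and by survival status, and read it together with ICU and hospital mortality.

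The cost is about one sentence in the analysis plan. No new procedure appears to be needed: length of stay already requires the end of each stay, and the Data collection section records death in the ICU and in hospital. The downside is that the tested quantity is no longer pure bed-days and partly repeats the mortality comparison.

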Potassium is the main intracellular cation of the body. The intracellular to extracellular potassium ratio affects both the fluid balance and the resting membrane potential. The reference plasma potassium ranges from 3.5 to 5.0 mmol/L. Levels below 3.0 mmol/L or above 6.0 mmol/L can cause serious symptoms of which cardiac arrhythmias are the most frequently observed [4]. After cardiac surgery (especially valvular surgery) postoperative atrial fibrillation is one of the most common complications with a reported incidence of 10-50%. It is associated with adverse outcome and despite new treatment strategies the incidence remains high [23-26]. After a potassium load, the intracellular compartment acts as the primary buffer. A potassium shift from extracellular to intracellular is caused by increased activity of the Na-K-ATPase pump, which can be directly stimulated by an increase in plasma potassium, insulin, catecholamines, aldosterone and alkalosis [27-29]. The most important organs in the homeostasis of potassium are the kidneys as they normally excrete or reabsorb potassium according to the overall potassium balance [30]. There is some evidence that a normal-high plasma potassium level is preferable in several cardiovascular states [31-33]. However, the optimal potassium level in the critically ill patient, who may be especially prone to the adverse effect of potassium derangements, has never been investigated prospectively. A cautious approach towards finding best target levels for potassium seems justified given the problematic discussions over optimal glucose targets in ICU patients [10,12]. A computer-assisted potassium regulation program such as GRIP-II provides the opportunity to perform a clinical trial to safely and efficiently compare two potassium targets within the normal range.

In this prospective phase 4 trial we will compare the effect of two different potassium control-target values that are both within the reference range of 3.5 - 5.0 mmol/L. In the NLP (Normal-Low Potassium) trial arm a normal-low potassium level of 4.0 mmol/L is aimed for, while in the NHP (Normal-High Potassium) trial arm a normal-high potassium level of 4.5 mmol/L is aimed for. We hypothesize that both physiological and pathophysiological differences may exist between the normal-low and the normal-high potassium control targets. In the study all patients are allocated to either the 4.0 or 4.5 mmol/L control target in alternating blocks of patients.

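### The subgroup sentence sets patient types against each other rather than NHP against NLP, and on either reading the tests the article states do not assess whether the target effect differs by AFF history or bypass use

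*Protocol article*

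**What the plan says.** The objective in the Background is a comparison of arms: "we will compare the effect of two different potassium control-target values".

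The Secondary endpoints section closes with a subgroup statement. Besides the cardiac surgery and total populations, it says that "the following subgroups will also be compared". Two items come after it. The first concerns the surgical technique: "Patients who underwent CABG with the use of cardiopulmonary bypass versus patients who underwent CABG without cardiopulmonary bypass". The second concerns earlier arrhythmia and has the same form: "Patients with a history of AFF prior to surgery versus patients without a history of AFF prior to surgery". Neither item names NLP, NHP or an endpoint.

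The Statistical analysis section offers Student's t test, the Mann-Whitney U test and, for outcomes such as AFF, this: "Fisher's exact test (categorical variables) will be used when appropriate". Significance is two-sided P<0.05. On interactions it says: "In multivariate analysis we will investigate the interaction with glucose, the amount of administered insulin, sodium and magnesium". AFF history and bypass use are not in that list.

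**The concern.** Subgroup analysis in a two-arm trial should show whether the effect of the intervention is similar across types of patient. Setting patients with an AFF history against patients without one does not do that. It shows how prognosis differs between patient types, a difference that allocation did not create and that can be the same whatever the targets do.

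If the authors instead mean arms compared within each subgroup, one P value per subgroup invites the conclusion that the higher target works in one group only. That pattern arises often by chance when the effect is in fact common to both groups.

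The article does address interaction, but it names other variables. Administered insulin accrues after the target has been assigned at ICU admission, and insulin requirements are also a listed secondary endpoint. For patients admitted after surgery, AFF history and bypass use are fixed before allocation, so they are the cleaner candidates for effect modification.

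**Working it through.** **1. The design inputs reproduce.** From Sample size calculation: 50% AFF in the pilot, a 10% reduction, two-sided 5%, 80% power, 2 × 400. Taking the reduction as absolute (50% to 40%), the two-proportion formula gives 388 per arm, or 408 with continuity correction, against 400 stated. Power at 400 per arm is 81%. A relative reduction (50% to 45%) would need 1565 per arm, so the absolute reading is the intended one. No stated figure is disputed.

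**2. Literal reading: subgroup against subgroup.** Two invented patterns of AFF incidence, with equal arms:

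| Pattern | History, NLP/NHP | No history, NLP/NHP | Target effect (history; no history) | History minus no history, arms pooled |
|---|---|---|---|---|
| A | 70% / 60% | 45% / 35% | 10; 10 points | 65 − 40 = 25 points |
| B | 65% / 65% | 50% / 30% | 0; 20 points | 65 − 40 = 25 points |

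The effects are identical across subgroups in A and very different in B, yet the subgroup contrast is 25 points in both. It carries no information on effect modification.

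**3. Alternative reading: NLP against NHP within each subgroup, tested separately.** The documents give no subgroup sizes. Assume AFF history splits the 800 evenly (200 per arm in each subgroup), patients are independent, and the 50% to 40% effect holds in both.

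- Normal approximation: Φ((0.10 − 1.96·√(2·0.45·0.55/200)) / √((0.25 + 0.24)/200)) = Φ((0.10 − 0.0975)/0.0495) = 52%.
- The planned Fisher test, by exact enumeration: 48%.
- Probability that exactly one of the two is significant: 2 × 0.48 × 0.52 = 50%.
- With no effect (50% in every group), the Fisher test's actual size is 4.0%, so the same probability is 2 × 0.040 × 0.960 = 7.7%.

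Other splits, by normal approximation:

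| Smaller subgroup's share | Power, smaller | Power, larger | Exactly one significant |
|---|---|---|---|
| 10% | 14.3% | 77.1% | 0.143·0.229 + 0.771·0.857 = 69% |
| 20% | 24.4% | 72.1% | 0.244·0.279 + 0.721·0.756 = 61% |
| 30% | 34.3% | 66.3% | 0.343·0.337 + 0.663·0.657 = 55% |
| 50% | 52.0% | 52.0% | 2·0.52·0.48 = 50% |

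The even split gives the lowest probability in the table.

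**4. What an arm-by-subgroup test could detect.** On the risk-difference scale, SE = √(0.49/n₁ + 0.49/n₂), where n₁ and n₂ are the per-arm sizes of the two subgroups. The smallest difference in effects detectable with 80% power is 2.8 × SE.

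- 50:50 (200 and 200): SE = 0.070, so 2.8 × 0.070 = 19.6 points.
- 20:80 (80 and 320): SE = 0.0875, so 2.8 × 0.0875 = 24.5 points.

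For a 10-point difference in effects, power is 14% at a 10% share, 21% at 20%, 26% at 30% and 30% at 50%.

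**5. Bypass use.** This factor covers CABG patients only, whereas the 800 also include valve surgery without CABG. Their number is not given, so the figures above do not carry over. Precision there is lower.

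**The case against.** The strongest reply is that the literal reading is not what the authors mean. The lead-in places the two subgroups alongside the cardiac surgery group and the total group, which throughout the endpoint list are populations in which outcomes are assessed by arm. On that view, the word versus merely lists the levels of a factor. This is plausible, and a reader should not take it as settled that the trial will compare patient types and ignore the arms. The wording is ambiguous. The plausible reading does not remove the difficulty, however, because the tests stated for comparing groups would still give one P value per subgroup.

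A reader might also infer that no arm-by-subgroup test is planned, or that interactions are restricted to the four named variables. The documents do not support this. The list is not described as exclusive, the article is condensed, and a full protocol or analysis plan may add terms. The point rests on what the article does state: which contrasts, which tests and which interaction variables.

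Nor does it follow that the trial cannot answer the question. Data collection covers medical history and bypass time, so the interaction can be estimated. The real limit is power, and the proposed test would seldom settle the matter either. That is a reason for an exploratory label, not for relying on separate tests.

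Two narrower replies also stand. The article does not say when glucose, sodium or magnesium is measured for the multivariate analysis, so only administered insulin is clearly post-allocation. And neither subgroup bears on the primary analysis.

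**Conclusion.** The point holds as a defect of wording and method in a secondary analysis. As written, the subgroup contrasts do not concern the targets. On the more generous reading, the stated tests do not assess whether the effect differs, and the named interactions leave out the two factors singled out as subgroups.

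For AFF history, with a common 50% to 40% effect, the chance of a significant result in exactly one subgroup is about 50% with Fisher's test at an even split, and rises to about 69% (normal approximation) when the smaller subgroup is 10% of the total. With no effect it is about 8% at the even split. The smallest interaction detectable with 80% power, about 20 to 24.5 points, is at least roughly twice the planned main effect. These figures rest on assumed subgroup shares, 2 × 400 patients and independence between patients, and they do not apply to bypass use. The change is worth making, but the primary conclusion does not depend on it.

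**What to change.** Replace the subgroup sentence and its two items with wording such as: NHP will be compared with NLP on the primary endpoint within each level of (i) bypass use among CABG patients and (ii) AFF history before surgery; effect modification will be tested by an arm-by-subgroup term in a logistic model that respects the allocation blocks; these analyses are exploratory.

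Report the effect estimate and confidence interval in each level beside the interaction test, and draw no conclusion from one level being significant and the other not. If a fuller plan already contains such a test, aligning the article's sentence with it is enough.

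The cost is one sentence and two extra model terms, using data the trial already collects. The downside is low power for interaction, hence the exploratory label.
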